### Participating services and eligibility

#### Recruitment

This trial will recruit whole services (no clients will be recruited). ACCHSs across Australia will be recruited based on expression of interest after circulation of study information to eligible services. A mix of services will be approached (by [name], BH or KC) with a range of remoteness as determined by the Australian Standard Geographical Classification—Remoteness Area (ASGC-RA).^35^ Both verbal and written information will be shared. Face-to-face meetings will be offered to eligible services. Indigenous project staff will be employed in recognition of their specialist skills and knowledge of working with ACCHSs. Additional time will be factored into project timelines for engaging with ACCHSs, including liaising with multiple key staff, follow-up conversations and knowledge translation of research documents.

#### Inclusion criteria

Services eligible for the trial will meet the following criteria:

Are an ACCHS.Provide care to 1000+clients per annum.Use Communicare as their practice software.

#### Exclusion criteria

Services will only be excluded if signed institutional consent forms are not returned before the close of recruitment. Data from clients aged 15 or under will not be extracted.

### Consent

After written institutional consent is signed, a memorandum of understanding will be negotiated by the senior investigator (KC) and lead author ([name]) with each ACCHS. Staff participating in individual qualitative interviews will also provide informed consent. Further consent will be sought, following completion of the main trial, if the authors wish to perform ancillary studies using stored data.

### Randomisation

ACCHSs will be categorised into three strata based on their remoteness using ASGC-RA^35^ : (1) urban and inner regional; (2) outer regional and remote; (3) very remote. Service names will be replaced by consecutive numbers. Within each stratum, half the services will be randomised by a computer program into the early support arm and half into the late support arm. Randomisation will be conducted by an author (TD) who is blind to services’ names.

#### Sample size

Sample size requirements were calculated using PASS (Power Analysis and Sample Software).^36^ Because larger numbers are needed to be able to determine increases in treatment provision than to demonstrate an increase in screening, the treatment provision outcome was used for sample size calculation. In an ACCHS of 1000+clients per year, approximately 60% (n=600) are likely to be aged 16 years or older.^37^ We estimate that 57% of clients (n=342) have likely been screened for alcohol use within 12 months^16^ and at least 25% (n=86) of screened clients are likely to be drinking above NHMRC recommended limits.^14 38 39^ In the late support arm, it is likely that 60% (n=51) of identified unhealthy drinkers will have an alcohol intervention recorded.^16^ Assuming an intra-cluster correlation coefficient of 0.04,^40 41^ enrolling 10 early support services and 10 late support services will allow for an increase in treatment provision over a 12-month period of at least 13% in the early support services to be detected (ie, from 60% to 73%; 80% power and 2-sided significance of 0.05). We will enrol an additional service in each arm to allow for the possibility of clusters dropping out of the study. Accordingly, the target number of services to be enrolled is 22.

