The primary outcome will be routinely collected data on screening rates using AUDIT-C. Secondary outcomes will include recorded delivery of brief intervention, counselling or prescribed medicines to reduce relapse in alcohol dependence. We will also describe changes in reported drinking and in biological measures that can be affected by drinking such as gamma glutamyltransferase (GGT, a liver enzyme),^33^ HbA1C^34^ and systolic blood pressure (BP).^34^

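### The stated 80% power for 60% to 73% refers to identified unhealthy drinkers, a group that support may enlarge, while treatment is analysed per attending client, so the power figure does not describe the planned analysis

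*Protocol article*

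**What the plan says.** The Sample size section uses treatment provision, a secondary outcome, to size the trial, on the ground that it needs larger numbers than screening does. It builds the planning figure as a chain for one service: 600 clients aged 16 or over, 57% screened for alcohol use within 12 months (342), at least 25% of those above recommended limits (86), and, in the late support arm, "60% (n=51) of identified unhealthy drinkers will have an alcohol intervention recorded". With an ICC taken as 0.04 and 10 services per arm, it states that the design "will allow for an increase in treatment provision over a 12-month period of at least 13% in the early support services to be detected". The proportions compared are 60% and 73%, and the calculation uses "80% power and 2-sided significance of 0.05". One spare service per arm brings the total to 22.

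The Overview states: "The primary outcome will be routinely collected data on screening rates using AUDIT-C". The abstract and the Overview both describe the support as intended to increase use of AUDIT-C as well as treatment.

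The Quantitative part of the Analysis section restricts analysis to Indigenous clients aged 16 or over who attended in the last 12 months. Within that population it lists the odds of a client being recorded as treated, and separately the number of clients identified with unhealthy use, by AUDIT-C and/or staff perception. It does not restrict the treatment outcome to identified drinkers.

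**The concern.** There are two connected difficulties.

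First, the powered proportion and the analysed proportion have different denominators: identified unhealthy drinkers in one place, attending clients in the other. The only detectable effect that the protocol states is thus on a scale its analysis section does not use.

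Second, the powered denominator is not fixed at randomisation. A client enters it by being screened and found to drink above limits, and the support is meant to raise screening. The calculation has one screening figure and one cluster size, with no allowance for a change in the early arm. If screening finds more drinkers there, the two arms' proportions describe differently selected clients, and the early arm's proportion can be diluted while more people are treated.

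At stake is whether the 80% figure can be relied on for the treatment outcome, and how a share treated among identified drinkers would be read if it were reported by arm.

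**Working it through.** **Inputs from the protocol (Sample size):** 600 adults per service; 57% screened; 25% of screened above limits; 60% v 73% treated; ICC 0.04; 10 services per arm; two-sided 0.05.

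**Assumptions not in the protocol:** early-arm screening of 77%; the treatment rate r among newly found drinkers; ICC 0.01; use of ICC 0.04 on the per-adult scale.

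**Method:** normal approximation, unpooled variance, power = Φ(|p2 − p1|/SE − 1.96), with effective n per arm = 10m/[1 + (m − 1)ICC].

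**1. The plan's own figure.**
- Chain: 600 × 0.57 = 342; 342 × 0.25 = 85.5 (stated as 86); 0.60 × 85.5 ≈ 51.
- m = 86: design effect 1 + 85 × 0.04 = 4.40; effective n = 860/4.40 = 195.5.
- SE = √[(0.60×0.40 + 0.73×0.27)/195.5] = 0.0473; power = Φ(0.13/0.0473 − 1.96) = 78.5%.
- With pooled variance, power is 77.9% and the difference detectable with 80% power is 13.3 points.

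The stated figure is reproduced closely with 86 per service, so the powered denominator is the identified drinkers. The arithmetic is sound on its inputs.

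**2. The same scale if screening rises to 77%.**
- Identified in the early arm: 600 × 0.77 × 0.25 = 115.5, that is 30 more than 85.5.
- Those who would have been found anyway are treated at 73%: 85.5 × 0.73 = 62.4.
- Ratio = (62.4 + 30r)/115.5.
- Effective n: control 855/4.38 = 195.2; early 1155/5.58 = 207.0.

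| r in new cases | treated per service | ratio | power v 60% |
|---|---|---|---|
| 73% | 84.3 | 73.0% | 79% |
| 60% | 80.4 | 69.6% | 53% |
| 40% | 74.4 | 64.4% | 15% |
| 20% | 68.4 | 59.2% | ratio below control |

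The ratio drops below 60% only if r < (0.60 × 115.5 − 62.4)/30 ≈ 23%. In every row more clients are treated than the 51 in the control arm.

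**3. The scale of the analysis section: treated per attending adult.**
- Baseline 51/600 = 8.5%. The planned gain with screening unchanged is 0.73 × 86 ≈ 63, so 63/600 = 10.5%.
- m = 600: design effect 24.96 at ICC 0.04 (effective n 240.4) and 6.99 at ICC 0.01 (effective n 858.4).
- SE at ICC 0.04 = √[(0.085×0.915 + 0.105×0.895)/240.4] = 0.0267; power = Φ(0.02/0.0267 − 1.96) ≈ 11%.
- At ICC 0.01, SE = 0.0141 and power ≈ 29%.
- Early-arm rate detectable with 80% power: 16.9% (ICC 0.04) or 12.6% (ICC 0.01).

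Step 3 keeps the 12-month window of the Sample size section. The analysis section's 2-month indicators are a further difference that is not costed here.

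**The case against.** The strongest reply is that the analysis section already uses a denominator that screening does not alter, so no planned test is exposed to dilution. That stands: the protocol does not say it will compare the arms on the share treated among identified drinkers. It answers the worry about a misread result, but it also confirms that the stated power belongs to a different quantity.

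A reader might infer more than the documents support:

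- **That the stated effect fails whenever support works.** It does not. Support also targets treatment, and if new cases are treated at 73%, power stays at about 79%.
- **That success would look like harm.** At 77% screening this needs new cases to be treated at under about 23%. A ratio as low as 54% (62.4/115.5) would need essentially none of the 30 new cases to have any intervention recorded. The protocol gives no such rate.
- **That each rise in AUDIT-C use adds identified drinkers one for one.** The 57% covers any alcohol screening, and identification may rest on staff perception. AUDIT-C may partly replace screening that already happens.
- **That the per-adult scale has more power.** In the 77% scenario with r = 60%, 80.4/600 = 13.4% are treated. Power is then about 41% at ICC 0.04, below the 53% for the ratio, or about 90% at ICC 0.01. The reason to use this scale is that it matches the analysis and is unaffected by screening.

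The 11% and 29% in step 3 likewise apply to the planned gain with screening unchanged. They are not a forecast of the trial's power.

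**Conclusion.** The point holds in a limited form. The calculation is right on its inputs, but its result (80% power for 60% to 73%) is for treatment among identified drinkers and does not describe the planned analysis per attending client. On its own scale it is conditional on unchanged identification, or on new cases being treated at about 73%. Under the assumed 77% screening, power for the ratio ranges from about 79% down to 15% as treatment of new cases falls from 73% to 40%.

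On the analysed denominator, the rise detectable with 80% power is from 8.5% to about 17% (ICC 0.04) or about 13% (ICC 0.01). The 77%, the rates in new cases, the ICC of 0.01 and the transfer of 0.04 to an outcome near 8.5% are all assumptions. The finding concerns a secondary outcome. It does not show that the primary screening outcome is underpowered, nor that any planned analysis is biased.

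**What to change.** In the Sample size section:

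- Restate the treatment target and detectable effect per attending adult aged 16 or over, as in the Quantitative analysis section: baseline 51/600 = 8.5%, with the rise detectable by 10 services per arm shown across a stated ICC range such as 0.01 to 0.04.
- Keep 60% to 73% only if it is labelled as conditional on similar identification of unhealthy drinkers in both arms.
- State that any reported share treated among identified drinkers is descriptive.

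The cost is a rewritten paragraph and a less favourable stated detectable effect. The number of services enrolled does not change.

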**Trial registration number:**

ACTRN12618001892202; Pre-results.

Strengths and limitations of this studyThis large cluster randomised controlled trial provides the power to test whether a model of support for Aboriginal and Torres Strait Islander primary care services can increase rates of alcohol screening and treatment provision.The protocol has been designed to be compatible with cultural context and to integrate western knowledge with the expertise and holistic approaches of these services.The use of regular data feedback and nomination of service champions offers the services an opportunity to be involved in ongoing quality improvement on alcohol care.The resultant study will be able to use routinely collected outcome data but this relies on the accurate recording of screening and alcohol care provided to clients.

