WorkshopsA national workshop will be held at the beginning of each support phase to bring champions from those services together for capacity building and networking. Feedback will be obtained from champions about pre/post-workshop knowledge, training preferences, priority areas for support and useful resources. Key presentations from workshops will be video-recorded and made available via a password-protected website.A wrap-up workshop will be organised for early support service champions (only) at the end of their support phase. Opportunities will be provided for service champions to provide verbal and written feedback on support, to discuss continuing quality improvement approaches and to network. Study results to that point will be discussed.Onsite trainingTraining will be offered at each service for all staff, with maximum duration of 2 days. Core elements will include screening, alcohol and the body, brief intervention and treatment approaches, including relapse prevention medicines. Due to the individuality of each service, flexibility will be given to allow inclusion of other (alcohol-related) training topics. The training will be co-facilitated by an addiction specialist (KC) and an Aboriginal researcher with clinical background ([name]) and will use culturally specific content and resources. Training content will be aligned with Indigenous protocols such as gender appropriateness, kinship systems and cultural obligations; such a family and community sharing which at times can impact on substance use.^27 44^ Pre/post-training feedback will be collected from participants.Resources/fundingThe trial will provide several hard copy and electronic resources for free to services (ie, the Handbook for Aboriginal Alcohol and Drug Work,^45^ Alcohol Awareness Kit^46^ and Quick Reference Guide to the Treatment of Alcohol Problems^47^).Each ACCHS will be provided with funding to purchase additional resources. Services can choose, in partnership with the chief investigators, how they spend their funding. The early support arm of the project will receive up to $9000 for resources. The late support arm will receive up to $3500. This is a reduced sum as they will have access to resources developed within the early support phase, so time and development costs will be less. Resources must be alcohol-related and may include additional training, conference attendance, education resources for staff or clients, funds for health promotion events or for local adaptation of resources.Practice software supportA Communicare support officer will be available during the trial to support ACCHSs with the practice software. Some ACCHSs may choose to make modifications to Communicare to make alcohol ‘clinical items’ more accessible for staff. One example is adding AUDIT-C into the Aboriginal and Torres Strait Islander (Indigenous) health assessment (‘Adult Health Check’), which was not routine in standard versions of Communicare at the time of trial commencement. AUDIT-C can also be added to other regular assessments such as antenatal and the pre-consult examination (ie, routine observations and/screening by a nurse or Aboriginal health worker before seeing the doctor). Services will also be provided with information about existing fields (‘clinical items’) available on Communicare for recording episodes of alcohol care (education/advice; on-site counselling), which can then be retrieved by data extraction.Second monthly data feedbackIndividual services will receive feedback on their routinely collected data on alcohol care every 2 months during their support phase. Data will be represented visually using images and or graphs (figure 3) and be fed back to nominated staff, including champions. Services will be asked for feedback on the data representation early in the support phase and adaptions will be made as requested. Services will be encouraged to discuss the results among staff, to see if there are ways to further improve alcohol screening and treatment rates.Phone conferencesSecond monthly phone conferences will be organised for service champions. These will provide the opportunity for ACCHSs to network nationally. The champions will be split into two groups for the phone conferences, based on remoteness. During teleconferences, champions can discuss their data feedback, progress, successes, difficulties, helpful tools, resources or approaches.Online platformA password-protected web portal will allow ACCHS staff to access and share current evidence, culturally appropriate resources and to network. It will include a discussion board. Short videos, training presentation slides and clinical protocols will be uploaded by project staff.

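### On the plan's own inputs, ten services per arm give about 78% power for 60% vs 73% (about 74% with a small-sample reference), so the stated 80% is modestly overstated

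*Protocol article*

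**What the plan says.** The Sample size section bases the calculation on treatment provision, a secondary outcome, and gives the reason: "Because larger numbers are needed to be able to determine increases in treatment provision than to demonstrate an increase in screening". It builds the cluster size in steps: 1000 or more clients per service, 60% of them adults (600), 57% of those screened (342), and then "at least 25% (n=86) of screened clients are likely to be drinking above NHMRC recommended limits". The control rate is "60% (n=51) of identified unhealthy drinkers will have an alcohol intervention recorded". The clustering input is a single value: "Assuming an intra-cluster correlation coefficient of 0.04". From these, 10 services per arm are said to detect a rise over 12 months "ie, from 60% to 73%; 80% power and 2-sided significance of 0.05". One service per arm is added for dropout, giving 22.

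The primary outcome is AUDIT-C screening. The section gives no effect size and no separate intra-cluster correlation (ICC) for it. The strengths and limitations box says that the trial "provides the power to test whether a model of support" can increase screening and treatment rates.

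**The concern.** Twenty randomised services are few. A large-sample (z) calculation treats the between-service variance as known, when in fact it is estimated from 20 units, so it tends to overstate power. The stated 80% is also the only power figure in the article, and the claim of adequate power in the strengths box rests on it.

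The primary outcome is covered only indirectly, by the assertion that it needs smaller numbers. With about 600 adults per service, power for screening is governed mainly by the ICC and the number of services. More clients per service therefore do not by themselves make screening the easier outcome. If either figure is taken at face value, a null result could be read as better powered than it was.

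**Working it through.** **Inputs** (Sample size section): 60% vs 73%; two-sided 0.05; k = 10 services per arm (11 enrolled); ICC 0.04; m = 86 per service (1000 × 0.60 × 0.57 × 0.25 = 85.5). Equal service sizes are assumed, because no spread is given.

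**Step 1. Effective sample.** Design effect = 1 + (m − 1) × ICC = 1 + 85 × 0.04 = 4.40. Effective n per arm = 10 × 86 / 4.40 = 195.5.

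**Step 2. Standard error.** √[(0.60 × 0.40 + 0.73 × 0.27) / 195.5] = √[(0.24 + 0.1971) / 195.5] = 0.0473. The standardised difference is 0.13 / 0.0473 = 2.75.

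**Step 3. The plan's figure by large-sample methods.** Unpooled: Φ(2.75 − 1.96) = 78.5%. With a pooled null variance it is 77.9%, and by arcsine 78.1%. The rate detectable with 80% power is 73.25% (unpooled) or 73.35% (pooled), a rise of about 13.3 points, which rounds to the stated 13. Services needed per arm for a strict 80%: 10.4 or 10.5, so 11.

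**Step 4. Small-sample reference.** Degrees of freedom = 20 − 2 = 18. A noncentral t with noncentrality 2.75 gives 73.9%. The detectable rate at 80% power is about 73.9%, a rise of about 13.9 points. Twelve services per arm would be needed to exceed 80% (82.1%).

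**Step 5. All 22 services retained.** Effective n = 11 × 86 / 4.40 = 215.0 per arm. Power is 82.2% (unpooled z), 81.7% (pooled z) or 78.3% (t, 20 df).

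**Step 6. Sensitivity to service size**, 10 per arm, by t on 18 df. The coefficient of variation (CV) of service size is assumed; the article gives none. Design effect = 1 + [(1 + CV²)m − 1] × ICC.

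| Mean m | Equal sizes | CV 0.4 | CV 0.6 |
|---|---|---|---|
| 86 | 74% | 69% | 63% |
| 200 | 79% | 74% | 68% |

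At an equal m of 300, power is 80.8%. By unpooled z, an equal m of 105 gives 80.1%.

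**Step 7. The screening premise.** Assume 600 adults per service and a 57% baseline. At ICC 0.04 the design effect is 1 + 599 × 0.04 = 24.96, and the effective n is 6000 / 24.96 = 240.4 per arm.

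| Assumed rise | Power by t (18 df) | Power by z | ICC above which screening needs more services than treatment |
|---|---|---|---|
| 10 points | 57% | 62% | 0.027 |
| 13 points | 81% | 84–85% | 0.047–0.048 |
| 15 points | – | – | 0.065 |
| 20 points | – | – | about 0.12 |

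For a 13-point rise the premise holds at ICC 0.04: 81–85% against 74–78% for treatment. For a 10-point rise it does not hold at that ICC.

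**The case against.** The strongest reply is that the stated figure is reproduced within rounding. The article names the software but not the test option. By z the shortfall is 1.5 to 2 points, and the detectable rise rounds to 13. A reader might infer that the calculation contains an arithmetic error; the documents do not support that. The 74% comes from a choice of reference distribution, and the Analysis section plans multi-level logistic regression without naming an 18-df test. This stands as a description of where the gap arises. It does not remove the gap: the planned model must still estimate between-service variation from about 20 services, and no two-sided variant computed here reaches 80% at 10 services of 86.

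Second, 86 is a floor, since both the client count and the 25% are stated as minimums. That also stands, and larger services raise power. With 10 equal services per arm, however, power by t is still about 79% at 200 per service. A reader might quote 63–69% for unequal sizes. Those figures rest on assumed CVs and take the floor of 86 as the mean, so they show direction only.

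Third, a reader might infer that the screening premise is false, or true only below an ICC of about 0.048. That threshold borrows a 13-point rise from the treatment outcome; it moves from 0.027 to about 0.12 for rises of 10 to 20 points. The 57% is any alcohol screening within 12 months, from four services in 2007, whereas AUDIT-C in the adult health check is something "which was not routine in standard versions of Communicare at the time of trial commencement". A lower AUDIT-C baseline makes the premise safer, not weaker: for a 13-point rise at ICC 0.04, power by z is about 90% from a 20% baseline and 97% from 10%. Nothing in the article supports a screening ICC as high as 0.10.

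**Conclusion.** The concern holds in a limited form. For 60% vs 73% with 10 equal services of 86 per arm and ICC 0.04, power is about 78% by the large-sample formula and about 74% with an 18-df reference, against the stated 80%. The large-sample gap alone would be rounding. The small-sample gap is material but modest, equivalent to a detectable rise of about 13.9 points in place of 13. Retaining all 22 services gives about 82% (z) or 78% (t), so by the t reference the two spare services do not restore 80% at 86 per service.

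The screening premise is not contradicted by the article's inputs. It is asserted without the effect size and ICC that decide whether it is true, and it should be qualified rather than withdrawn. The absence of a separate screening calculation is, by itself, mainly missing detail in a condensed article.

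**What to change.** Restate the treatment figure: about 74% power for 60% vs 73%, or 80% power for about 60% vs 74%, with 10 equal services of 86 per arm, ICC 0.04 and a small-sample reference. Add that unequal service sizes reduce this, and that larger services or retention of all 22 increase it.

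Qualify the premise about screening by stating the rise and ICC for which it holds, for example a 13-point rise from 57% at ICC 0.04. As a secondary step, report the detectable AUDIT-C difference from the rate, ICC and service sizes in the 12-month baseline extraction, and bring the power statement in the strengths box into line.

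The cost is a few restated figures and a short calculation on data that the trial already plans to extract. No services need be added and the design does not change.
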